**Methods:**

The efficacy of inhaled loxapine and the alternative antipsychotic aripiprazole delivered via intramuscular (IM) injection will be compared in the Phase IIIb PLACID study. Adults (18–65 years) with a confirmed diagnosis of schizophrenia or bipolar I disorder presenting with acute agitation will be randomly assigned to open-label treatment in a 1:1 ratio. Clinical evaluation will be conducted by raters blinded to treatment assignment. The primary efficacy endpoint is time to response (defined as a Clinical Global Impression of Improvement [CGI-I] score of 1 [very much improved] or 2 [much improved]).

Secondary endpoints will include the percentage of responders at different time points after dosing; the proportion of patients who receive 1 or 2 doses of study drug; time to second dose; time to rescue medication; satisfaction with study drug (evaluated using Item 14 of the Treatment Satisfaction Questionnaire for Medication); and safety and tolerability. Approximately 360 patients will be recruited with an interim analysis conducted once 180 patients have completed the study to decide whether to stop for futility or continue with or without an increase in the sample size up to additional 288 patients.

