An interim analysis will be performed on the phase 1 data to determine whether to continue into phase 2 or to stop the trial due to futility or unfeasibility. The final sample size of the PLACID study will be re-calculated based on the interim analysis results. The two-phase design with interim analysis is justified due to the limited availability of CGI-I data during the first 2 h’ post-administration both for inhaled loxapine and IM aripiprazole, and therefore making difficult the sample size estimation. Data demonstrating meaningful improvements from baseline on the CGI-I scale at 120 mins post dose are available [15, 16, 20, 22] for both treatments, but data demonstrating the time course of these improvements during the first two hours of treatment, when rapid and effective action is required to minimise the risks associated with acute agitation, are lacking.

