### Statistical analysis

The primary endpoint “time to response” is defined as the first time point in minutes after Dose 1 at which CGI-I score of 1 or 2 is achieved during the 120 min after the first dose. The comparison of time to response between the two treatment groups will be performed using a Wilcoxon rank-sum test with a two-sided significance level of 0.05. Patients without response within 2 h will be considered as non-responders and the ‘time to response’ as 4 h (2 h more than the maximum follow-up for this variable). The median difference (95% CI) will be estimated by means of the Hodges-Lehmann approach based on the Wilcoxon rank-sum (Mann-Whitney) distribution. Kaplan-Meier curves of time to response will also be presented by treatment group. Additionally, the Mantel-Haenszel log-rank test will also be conducted for sensitivity purposes.

Secondary analyses will be exploratory without formal sample size estimation. Safety and tolerability data will be presented descriptively.

A total sample size of 180 in each group will have approximately 90% power to demonstrate superiority of inhaled loxapine versus IM aripiprazole for the primary efficacy endpoint at a one-sided significance level of 0.025. If the interim analysis suggests that more than 30% additional patients are required at 0.025 one-tailed alpha level and approximately 90% power, it will be considered if it is feasible to include >30% additional patients. Since there will be neither stopping for overwhelming efficacy, nor is there a situation where the sample size will decrease based on the interim analysis results, the alpha level will be preserved.

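### No efficacy stop and no decrease in sample size do not by themselves preserve alpha for the ordinary final Wilcoxon test; one-sided alpha can modestly exceed 0.025, depending on rules the article does not give

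*Protocol article*

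**What the plan says.** The primary comparison is made "using a Wilcoxon rank-sum test with a two-sided significance level of 0.05". The sizing statement reads: "A total sample size of 180 in each group will have approximately 90% power to demonstrate superiority", and it is made "at a one-sided significance level of 0.025". The two levels agree, since both use the critical value 1.960.

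The Abstract describes "an interim analysis conducted once 180 patients have completed the study", at which the trial may stop for futility or go on, with up to 288 additional patients. The Design section adds: "The final sample size of the PLACID study will be re-calculated based on the interim analysis results". The Statistical analysis section sets a target of about 90% power. If more than 30% extra patients would be needed, "it will be considered if it is feasible to include >30% additional patients".

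On type I error the article gives one argument: the trial cannot stop early for a positive result, "nor is there a situation where the sample size will decrease based on the interim analysis results, the alpha level will be preserved".

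**The concern.** The two conditions deal with two known routes to inflation: rejecting early, and cutting the sample when the interim result looks good. They leave a third route open. If N is raised after a weak stage 1, the ordinary pooled test gives that weak stage less weight than planned. Under the null hypothesis this raises the chance of a final rejection. Fixed stage weights, a limit on when N may be raised, or a sufficiently strict binding futility stop would close this route. The article rests its claim on none of these.

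The level of the single confirmatory comparison is at stake. The Abstract says that a significantly shorter time to response could support inhaled treatment as standard of care.

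**Working it through.** **Inputs**
- Interim at n1 = 180 of 360 patients (Abstract; Statistical analysis): information fraction 180/360 = 0.50.
- Critical value 1.960; target power 90%, so 1.960 + 1.2816 = 3.2415.
- Maximum N: 288 more patients can be read as 180 + 288 = 468 (exactly 1.30 × 360) or 360 + 288 = 648. Both were run.
- Assumption: N is recalculated from the treatment comparison at the interim. The article implies this but does not say it.

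**The plan's own figure.** No effect size is given (the Design section says the lack of CGI-I data was "therefore making difficult the sample size estimation"), so 180 per group at 90% power cannot be reproduced. Back-solving Noether's formula, 360 = 3.2415² / [3(p − 0.5)²], gives p = 0.599 for the probability of a shorter time on loxapine. The type I error below does not depend on p.

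**Formula.** Under the null, z1 and z2 are independent standard normal. The ordinary final statistic is Z = √(180/N)·z1 + √((N − 180)/N)·z2. Given z1, the chance of rejection is

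CE(N, z1) = 1 − Φ[(1.960√N − √180·z1)/√(N − 180)],

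and alpha is the integral of CE(N(z1), z1)·φ(z1) over z1.

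**Mechanism**
- At z1 = 0 the argument is 1.960·√(N/(N − 180)). N = 360, 468 and 648 give CE = 0.0028, 0.0062 and 0.0105: raising N raises the error.
- At z1 = 2 the same three sizes give 0.220, 0.179 and 0.143: raising N lowers it.
- Setting the derivative in N to zero gives z1 = 1.960·√(180/N), which is 1.386 at N = 360. At or above 1.386, no increase can raise CE.
- Conditional power at the interim estimate with N = 360 is 1 − Φ(1.960√2 − 2·z1). It equals 50% at the same value, z1 = 1.386.

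**Recalculation rule.** Required N = 180·(3.2415/z1)², set to the maximum if z1 ≤ 0, and held between 360 and the maximum. Required N exceeds 468 when z1 < 2.010, and 648 when z1 < 1.708.

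| Rule (ordinary final test unless stated) | One-sided alpha, max 468 | max 648 |
|---|---|---|
| N fixed at 360 | 0.0250 | 0.0250 |
| Recalculate to 90% power, no binding futility | 0.0264 | 0.0282 |
| Worst choice of N between 360 and the maximum | 0.0277 | 0.0304 |
| Recalculate, binding stop at z1 < 0 | 0.0255 | 0.0262 |
| Recalculate, binding stop at conditional power < 10% | 0.0216 | 0.0210 |
| Stay at 360 if required N exceeds the maximum | 0.0247 | 0.0238 |
| Stop if required N exceeds the maximum | 0.0075 | 0.0105 |
| Recalculate only at conditional power ≥ 50%, otherwise 360 | 0.0237 | 0.0230 |
| Fixed stage weights √0.5 and √0.5, any increase rule | 0.0250 | 0.0250 |

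Rows 2 and 3 meet both of the article's conditions and still exceed 0.025, which disproves the stated reason.

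**Check on the actual test.** A simulation of 2,000,000 trials used a tie-corrected Wilcoxon test and an assumed null distribution over the visit times, with 240 minutes for non-responders. It gave 0.0264 and 0.0281 for row 2, and 0.0277 and 0.0303 for row 3 (Monte Carlo standard error 0.0001).

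**Power, maximum 468.** The effect is the one implied by 90% power at 360, so z1 has mean 3.2415·√0.5 = 2.292. Integrating the same way with that shift gives 95.4% for the ordinary test, 95.1% with fixed weights, and 91.7% if N may rise only at conditional power of at least 50%.

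**The case against.** The strongest reply is that inflation has not been shown. The interim exists partly to stop for futility or unfeasibility, and a large increase is subject to a feasibility decision. Rules of that kind, if followed, remove the excess. Even a lax binding futility stop would do for the recalculation rule: z1 of about 0.17 to 0.26 is enough, which is a conditional power of only about 1%. Futility boundaries, conditional-power limits and stage weights are also details that a condensed article properly leaves to the full protocol or analysis plan.

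Much of this stands. A reader might infer that the design as described inflates alpha. The document does not support that, because the result turns on rules it does not state. A reader might also treat the clause on more than 30% extra patients as an unlimited maximum and quote larger errors. The only stated limit is 288 additional patients, so figures beyond 648 have no source. Use of the interim treatment effect is a strong inference, not a quotation; recalculation blind to the treatment difference would cause little or no inflation.

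The reply does not rescue the sentence itself. The article does not leave alpha control to another document. It asserts control and gives a reason, and that reason is insufficient. If a valid method exists elsewhere, the sentence misreports the basis for control.

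**Conclusion.** The stated justification is wrong as written: the two conditions do not guarantee the level of an ordinary Wilcoxon test when N can be raised from interim results. The possible excess is modest. Under recalculation to 90% power it is 0.0264 − 0.025 = 0.14 to 0.0282 − 0.025 = 0.32 percentage points one-sided. At worst it is 0.27 to 0.54 points. It is zero or negative under several rules that the text allows.

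This rests on re-estimation from the treatment comparison, an information fraction of 0.50, the normal approximation (checked by simulation) and a maximum of 468 or 648. It should be fixed because it concerns the one confirmatory test and the correction is cheap. The size of the excess does not make it a must-fix.

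**What to change.** Replace the sentence on preserved alpha with a method that does control it. Either of these would do:

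1. **Restrict the increase.** N may be raised only if conditional power at the interim estimate, with 360 patients, is at least 50% (z1 ≥ 1.386). The ordinary Wilcoxon test and the Hodges-Lehmann estimate stay as they are. Alpha is 0.0237 (maximum 468) or 0.0230 (maximum 648). The cost is that weaker interim results cannot be rescued: power at the implied planning effect is 91.7% with maximum 468.
2. **Fix the weights.** Compute the Wilcoxon z-statistic separately for the first 180 patients and for those enrolled later. Combine them with weights √0.5 and √0.5, and reject above 1.96. Alpha is 0.025 under any increase rule. Show the pooled Wilcoxon and Hodges-Lehmann results as supportive. The costs are about a third of a percentage point of power (95.1% against 95.4%), unequal weighting of patients if N grows, and a Hodges-Lehmann interval that may not match the test exactly.

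In either case, state the increase rule, the maximum total N, whether the recalculation uses the treatment comparison, and whether the futility stop is binding. If the full protocol or analysis plan already contains such a method, the sentence should cite that as the reason. The change is to wording only.

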## Discussion

Acute agitation in patients with psychiatric disorders including schizophrenia and bipolar disorder is a serious complication with the potential to escalate rapidly to aggression and physical violence [3, 5, 6]. Early recognition of the onset of acute agitation and intervention to rapidly calm the agitated patient without over-sedation are the main goals of the pharmacological management of such patients [3]. Antipsychotic medications are widely used in this setting and IM delivery provides a more rapid onset of effect compared with oral formulations. However, IM delivery of medication in this setting may not be optimal for patients already in an agitated state and may interfere with the therapeutic relationship between the patient and their carers [2]. Inhaled formulations have the potential to provide a more rapid onset of effect than IM injection. The medication is delivered through the lung with rapid transition to the systemic circulation via a non-coercive, non-invasive route of administration [3, 25]. Clinical evaluation of the inhaled antipsychotic loxapine has demonstrated an onset of therapeutic effect as early as 10 min after dosing, an effect that is maintained through 24 h among patients with acute agitation and schizophrenia or bipolar disorder [15, 16, 21, 26].

The PLACID trial will assess the efficacy and safety of inhaled loxapine compared with the IM antipsychotic, aripiprazole, in acutely agitated patients with schizophrenia or bipolar disorder. The PLACID trial is planned as a pragmatic trial close to the real world setting.

The CGI scale, which was developed as a brief, stand-alone assessment of the patient’s global functioning prior to and after initiating a study medication, will be used to assess the primary endpoint. This is a simple instrument widely used in a clinical practice and can be completed in less than a minute by an experienced rater [27] Even if not validated for agitation assessment, it was shown that there is a very good correlation between the CGI and PANSS-EC [28]. All raters will be trained in the proper CGI use to assess the agitation grade.

Both inhaled loxapine and IM aripiprazole are currently available in Europe for the treatment of acute agitation in patients with schizophrenia or bipolar disorder.

REMS (Risk Evaluation and Mitigation Strategy) is necessary with inhaled loxapine to mitigate the risk of bronchospasm. For this reason, only the centers with immediate access on site to supplies and personnel trained to manage acute bronchospasm will participate in this study. REMS is the strategy to manage a known or potential serious risk associated with a drug or biological product required by the US FDA (Food and Drug Administration).

The pharmacokinetic profiles (PK) of both drugs differ significantly and this is explained by the differences in the administration route. The peak plasma concentration of IM aripiprazole is achieved at 1 h, while for inhaled loxapine it is 2–3 min. Such a short time is explained by the fact that inhaled loxapine is directly absorbed into the blood stream with a PK profile similar to IV formulations. This study will prove if these differences in PK parameters correspond to clinical parameters, namely shorter time to response of inhaled loxapine.

Patients will be randomly assigned to treatment to avoid bias in terms of treatment allocation. The delivered treatment is necessarily open-label due to the different methods of administration. To avoid the issue of rater bias, drug administration and clinical evaluation will be carried out by different personnel, with the clinical rater blinded to treatment allocation and the randomization will be stratified by diagnosis to balance the groups. Patients will be instructed not to tell the treatment they receive.

## Conclusion

In conclusion, the prompt stabilisation of patients with schizophrenia or bipolar disorder presenting with acute agitation has the potential to facilitate a patient-centered management approach by maintaining the patient-physician relationship and minimising the need for physical or mechanical restraint or sedation [2, 3]. The PLACID study will allow, for the first time, the direct comparison of the timing of the onset of therapeutic effect of an IM antipsychotic, aripiprazole, and an inhaled antipsychotic, loxapine, for the treatment of acute agitation in patients with schizophrenia or bipolar disorder. The results of this trial have the potential to change future treatment guidelines and have a powerful impact on clinical practice.

## Abbreviations

CGI-I: Clinical global impression of improvement
CGI-S: Clinical global impression of severity
DSM: Diagnostic and statistical manual of mental disorders
IM: Intramuscular
TSQM: Treatment satisfaction questionnaire for medication
WHO: World Health Organization
